### Randomisation

Participants will be randomised using an interactive web response system (eClinical OS™, Merge Healthcare, Morrisville, NC, United States). The randomisation lists will be prepared centrally by the contract research organization BioStata ApS, Birkerød, Denmark using a validated computer program. The randomisation will be stratified by bleeding volume (PPH: 700 to 1,000 mL or PPH >1,000 mL). Within each bleeding category, there will be a 1:1 randomisation ratio to one of the two treatment groups.

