### Statistical methods and data analysis

All tests are pre-specified in a statistical analysis plan. The primary analysis population will be the full analysis set, including all randomised participants who received the study drug and have at least one post-baseline physical fatigue score. The primary endpoint is the aggregated change in the physical fatigue score from baseline to week 12. This will be calculated as the area under the curve of the changes in the physical fatigue score from baseline to each visit until week 12, divided by the number of scheduled days (observation period). The area under the curve will be calculated using the linear trapezoidal method and scheduled days. The primary endpoint will be analysed using an analysis of variance model, with treatment and amount of PPH (700 to 1,000 mL or >1,000 mL) as factors, and baseline MFI physical fatigue score as the covariate. The estimated treatment differences (iron isomaltoside 1000 versus standard medical care) expressed as contrasts of the adjusted means will be presented with corresponding 95% confidence intervals and the *P* value. Iron isomaltoside 1000 will be considered superior to standard medical care if the lower limit of the 95% confidence interval is above zero. We will also perform a per protocol analysis excluding participants with major protocol deviations, such as rescue allogeneic RBC transfusion.

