All statistical tests of the efficacy endpoints will be two-sided and performed on a 5% significance level. Estimated treatment differences and 95% confidence limits will be presented together with the corresponding *P* value. Continuous secondary endpoints will be analysed by a mixed model for repeated measurements, including visit and treatment-by-visit, and PPH (700 to 1,000 mL or >1,000 mL) as factors, the baseline value as the covariate, and the subject as the random effect. If no baseline value is measured for the endpoint in question, the value at the first measured time will be included as the covariate. An unstructured covariance structure will be used to model the within-subject errors and the estimation method will be a restricted maximum likelihood-based approach. The analysis will be based on the ‘missing at random’ assumption and performed using the data from each observed case. ‘Proportion’ endpoints will be analysed by logistic regression with treatment as the factor. Where relevant, the baseline value of the parameter in question will be included as the covariate. Time to postpartum lactogenesis and time to discontinuation of breastfeeding will be assessed and analysed using Kaplan-Meier curves and compared between treatments using a log-rank test. The laboratory data will be analysed as described for the continuous variables above. Adverse events will be summary tabulated using the latest version of the Medical Dictionary for Regulatory Activities body system and preferred term indicating the number and percentage of participants and the number of events. The number of participants who experience an adverse drug reaction, including suspected unexpected serious adverse reactions, will be compared between treatment groups.

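### Logistic regressions omit the PPH stratum used at randomisation, and the log-rank tests name no strata: a minor, cost-free gain for secondary endpoints if blood loss is prognostic

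*Protocol article*

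**What the plan says.** All references are to the Methods/Design part of the protocol article.

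- **Randomisation.** "The randomisation will be stratified by bleeding volume", with two categories divided at 1,000 mL. "Within each bleeding category, there will be a 1:1 randomisation ratio to one of the two treatment groups".
- **Statistical methods and data analysis, primary endpoint.** The analysis of variance carries these terms: "with treatment and amount of PPH (700 to 1,000 mL or >1,000 mL) as factors, and baseline MFI physical fatigue score as the covariate".
- **Same section, continuous secondary endpoints.** The repeated-measures mixed model is specified as "including visit and treatment-by-visit, and PPH (700 to 1,000 mL or >1,000 mL) as factors, the baseline value as the covariate".
- **Same section, proportion endpoints.** These "endpoints will be analysed by logistic regression with treatment as the factor". The only addition is optional: "Where relevant, the baseline value of the parameter in question will be included as the covariate".
- **Same section, time-to-event endpoints.** Time to lactogenesis and time to stopping breastfeeding are shown as Kaplan-Meier curves and "compared between treatments using a log-rank test". Strata are neither named nor ruled out.

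The section also refers to a separate statistical analysis plan, which is not available here.

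**The concern.** Randomising 1:1 within blood-loss category forces that category into balance between the arms. If it also predicts the outcome, the treatment comparison varies less from trial to trial than under simple randomisation. An analysis that ignores the category takes no credit for this. Its test then rejects less often than 5% under the null and has less power than a stratified test on the same data.

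The article takes that credit in two of its models and not, as worded, in the others. The logistic wording is a positive specification: it names treatment as the single factor, in the same section that lists PPH category for the mixed model. The outcome's own baseline is no substitute. RBC transfusion, for instance, has no useful baseline, because women with a peripartum transfusion are excluded.

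At stake is precision on secondary efficacy outcomes such as transfusion, lactogenesis and duration of breastfeeding. The sample size was set on the primary endpoint alone, so these outcomes have no planned power in reserve.

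**Working it through.** **1. The plan's own figure.** The section on number of participants gives a difference of 1.8, SD 4.2, two-sided 5% and 80% power. By the normal approximation, n per group = 2 × (1.960 + 0.842)² × (4.2/1.8)² ≈ 85.5, so 86. The t-distribution version gives 86.4, so 87 as stated. With 13% dropout, 87 / (1 − 0.13) = 100 per group, or 200 in total. The figure reproduces. It concerns the primary endpoint, whose model already includes the stratum, so this point does not touch it.

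**2. Inputs for the secondary endpoints.** From the document: 200 women, 1:1 within two strata, two-sided 5%. Not in the document, and therefore assumed over a range: event rates, the share of women above 1,000 mL, the size of the stratum effect and the treatment effect.

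**3. Binary outcomes.** Two score tests were compared over 200,000 simulated trials per scenario: the score test from logistic regression on treatment alone, and the score test stratified by PPH category. The treatment odds ratio was 0.25 where the lower-stratum control risk was 10%, and 0.42 where it was 30%. Entries are power (%), treatment-only / stratified.

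| Control risk, lower stratum | Share >1,000 mL | Stratum OR 1 | OR 2 | OR 3 | OR 5 |
|---|---|---|---|---|---|
| 10% | 30% | 57.7 / 57.9 | 68.1 / 68.4 | 74.3 / 74.7 | 80.1 / 81.7 |
| 10% | 50% | 57.7 / 58.0 | 74.1 / 74.2 | 81.7 / 82.1 | 88.9 / 90.0 |
| 30% | 30% | 71.2 / 71.7 | 74.4 / 75.5 | 75.0 / 76.9 | 72.0 / 76.5 |
| 30% | 50% | 71.3 / 71.8 | 77.2 / 78.0 | 77.7 / 80.0 | 75.3 / 79.7 |

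The gain is 0.1 to 1.1 points at OR 2, 0.4 to 2.3 at OR 3 and 1.1 to 4.5 at OR 5. The 0.2 to 0.5 points seen at OR 1 show how small the OR 2 gains are. Null rejection by the treatment-only test is 4.7 to 5.0% at OR 2 and 3.8 to 4.0% at OR 5. The stratified test stays near 5%.

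**4. Log-rank test.** Exponential times were censored at 12 weeks, and the control event proportion is 1 − exp(−hazard × follow-up). For example, 0.02/day gives 1 − exp(−0.02 × 84) = 81%, and 0.004/day gives about 29%. Entries are power (%), unstratified / stratified. Where separate sets of runs used the same inputs, both results are shown as a range.

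| Control events, lower stratum | Share >1,000 mL | Treatment HR | Stratum HR 2 | Stratum HR 3 |
|---|---|---|---|---|
| nearly all (0.5/week) | 40% | 0.67 | 74.1 / 79.1 | 68.2 / 79.2 |
| 81% (0.02/day) | 50% | 0.65 | 73–74 / 78–79 | 65–68 / 80–81 |
| 45% (0.05/week) | 40% | 0.56 | 76.5 / 78.3 | 76.8 / 83.3 |
| 29% (0.004/day) | 50% | 0.50 | 74.9 / 76.2 | 80.6 / 83.9 |

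The gain is about 1 to 5 points at HR 2 and 3 to 15 at HR 3. It shrinks as events become rarer: at about 15% control events and a treatment HR of 0.40 it is 0.6 and 1.8 points. With 40% of women in the upper stratum, the unstratified test rejects a true null in 3.9 to 4.2% of trials at HR 2 and 3.3 to 3.7% at HR 3. The stratified test ranges from 4.5 to 5.9% over all stratum effects. At stratum HR 1 the two tests do not differ materially (for example 69.6 / 69.5).

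**5. The odds ratio itself.** Take control risks of 10% and 40% in equal strata, which is a stratum OR of (0.40/0.60) / (0.10/0.90) = 6, and a within-stratum treatment OR of 0.50. Treated risks are then 5.3% and 25%. Averaged over strata, treated risk is 15.1% and control risk 25%, so the unadjusted OR is (0.151/0.849) / (0.25/0.75) = 0.53. Every woman's stratum-specific effect is still 0.50. The two numbers answer different questions.

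**The case against.** **The stratum may not matter.** The article gives no reason for choosing this stratifier and no stratum-specific outcome data. It hypothesises that significant haemorrhage raises the risk of iron deficiency, but does not compare the two categories. It calls any link between iron deficiency anaemia and delayed lactogenesis unknown, and cites one retrospective association with breastfeeding duration. Eligibility also narrows the contrast, since women above 1,000 mL enter only with Hb above 6.5 g/dL. This stands: a reader might infer that power is certainly lost, or that blood loss was chosen because it predicts these outcomes, and the document shows neither. The Background does place the limit of what full iron stores can replace at 1,000 mL, the stratum boundary, so a prognostic effect is plausible.

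**Silence is not exclusion.** No strata are named for the log-rank test, but none are excluded, and the unseen analysis plan may stratify it. This also stands, and it matters because the larger figures belong to the log-rank test. It does not reach the logistic regressions, where the article states the model.

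**The odds ratio is not biased.** A reader might take the shift from 0.50 to 0.53 as bias toward 1. It is not. The treatment-only model validly estimates a marginal odds ratio and the adjusted model a conditional one.

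**The size depends on the event rate.** Gains of 13 to 15 points need a stratum HR of 3 and about 81% events in lower-stratum controls. That may suit lactogenesis but is only an assumption for stopping breastfeeding. This stands, and is why a range is given.

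**Conclusion.** The point holds as a minor one. The article randomises within PPH category and adjusts for it in two models, but states the logistic regressions without it and names a log-rank test without strata. The cost is mild conservatism and some lost power on secondary binary and time-to-event outcomes, conditional on the category being prognostic. At a stratum effect of 2, that is roughly 0 to 1 point for binary outcomes and 1 to 5 for the log-rank test. Larger losses need a strong stratum effect and, for the log-rank test, frequent events. All these sizes rest on assumed inputs, because the document supplies none.

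Nothing here supports a reading that the trial's main conclusion is at risk. The primary and continuous secondary analyses already include the stratum, and the error is in the conservative direction.

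**What to change.** - Add PPH category (700 to 1,000 mL or >1,000 mL) as a factor in the logistic regressions where event counts allow, and state in advance what will be done for outcomes with too few events, such as RBC transfusion.
- Specify the log-rank tests for lactogenesis and for stopping breastfeeding as stratified by PPH category. If the analysis plan already does so, only the article's wording needs completing.
- Label the reported odds ratios as conditional on PPH category, so that they are not read as marginal effects.

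The cost is a few lines of wording before analysis. No new data are needed, because the category is recorded for every randomised woman, and almost nothing is lost if it proves not to be prognostic. Fixing the choice now also removes a later choice between adjusted and unadjusted results in an open-label trial.

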### Outcomes and safety measures

The primary outcome is the aggregated change in physical fatigue score within 12 weeks postpartum, as measured by a subscale of the Multidimensional Fatigue Inventory (MFI) [37]. Secondary efficacy outcomes include changes in the Hb concentration, *p-*ferritin, *p-*iron, *p-*transferrin, transferrin saturation, reticulocyte count, mean reticulocyte Hb content, other MFI and Postpartum Questionnaire (PPQ) fatigue items, symptoms of postpartum depression, time of postpartum lactogenesis, time of discontinuation of breastfeeding and transfusion of allogeneic RBCs.

The safety outcomes are discontinuation due to intolerance, frequency, nature and severity of adverse events, vital signs, and *p*-sodium, *p-*potassium, *p-*calcium, *p-*phosphate, *p-*urea, *p-*creatinine, *p-*albumin, *p*-bilirubin, *p*-aspartate aminotransferase and *p*-alanine aminotransferase levels. Other outcomes are maternal milk iron level, anaemia symptoms and gastrointestinal symptoms.

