## Discussion

The aim of this study is to compare a new treatment option (iron isomaltoside 1000) to standard medical care. The choice of the latter active comparator, ‘the drug of first choice’, enables us to use the results of this study for assessing the potential additional benefit of iron isomaltoside 1000 in a clinical setting.

The standard medical care treatment group does not receive a general specified recommendation of oral iron supplementation. We considered that standard treatment, as defined by the individualised regimen chosen by the parturient and her midwife, was the proper comparator. A pregnant woman usually takes oral iron supplementation from early pregnancy and finds a preparation and a dose that is suitable for her. A general fixed regimen might cause gastrointestinal side effects in some individuals, and a possible insufficient effect in others. Therefore, the fixed regimen would be suboptimal as a comparator compared with the standard individualised regimen, which is current practice in the Capital Region of Denmark. The actual use of oral iron, including specific preparation, dose and duration of treatment, is registered at each follow-up visit.

The individualised regimen design implies that we were not able to blind the randomisation in this trial. Also, since iron tablets colour the stools, we assessed that a double-blinded design would be unfeasible and would not contribute additional scientific merit. Accordingly, most previously published randomised controlled trials with iron treatment of women after childbirth have not been double-blinded [23–27].

The strength of this trial is the fact that it will be conducted at a single centre. This means that the standard medical care is less diverse than it might otherwise be and we can ensure a full overview of all parturients with PPH ≥700 mL in the time period of inclusion, which will enable us to collect detailed information about those excluded and the reasons why not.

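### The only adverse-event category named for comparison between groups depends on an open-label causality judgement; all-cause adverse events should be compared as well (minor, cheap improvement)

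*Protocol article*

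**What the plan says.** Under Outcomes and safety measures, the Protocol article defines the safety outcomes without reference to causality: "The safety outcomes are discontinuation due to intolerance, frequency, nature and severity of adverse events, vital signs, and" a list of blood chemistry and liver values. Adverse drug reactions are not named there as an outcome.

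Under Statistical methods and data analysis, adverse events are handled in two sentences. The first covers events of any cause: "Adverse events will be summary tabulated using the latest version of the Medical Dictionary for Regulatory Activities body system and preferred term", with numbers and percentages of participants and numbers of events. The second states the comparison: "The number of participants who experience an adverse drug reaction, including suspected unexpected serious adverse reactions, will be compared between treatment groups". No test or estimate is named for it.

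Other safety data are treated separately: "The laboratory data will be analysed as described for the continuous variables above". That refers back to the model for continuous endpoints: "Continuous secondary endpoints will be analysed by a mixed model for repeated measurements, including visit and treatment-by-visit".

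On the conditions under which causality would be judged, the Study design section calls the trial open-label, and the Discussion says "we were not able to blind the randomisation in this trial". On the control regimen, the Discussion says "The standard medical care treatment group does not receive a general specified recommendation of oral iron supplementation". The Intervention section describes standard care as typically oral iron, with varying dose and duration, and has actual use recorded at each follow-up visit.

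**The concern.** The declared safety outcome covers all adverse events, but the stated comparison covers only the subset that passes a relatedness filter. A comparison of that subset is fair only if the filter works in the same way in both arms, and three features of this trial make that uncertain.

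- Whoever judges relatedness can know the arm.
- One arm has a single supervised infusion at a known time. The other has an individualised oral regimen, often begun in early pregnancy and so before randomisation. The two exposures do not prompt attribution equally.
- The article does not say against which drug an event in standard care is judged. The term study drug appears in the definition of the full analysis set without being defined by arm.

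The Discussion accepts the risk of open-label bias for the subjective fatigue endpoint but does not extend it to this judged safety category. What is at stake is how the safety results are read: a difference in reactions could reflect attribution rather than risk, or attribution could hide a real difference. The primary result is not affected.

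**Working it through.** The article gives no adverse-event rate for this trial and no attribution rate, so there is no safety figure to reproduce. The check is a reading of the text, followed by an illustration on assumed figures.

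**What is compared, category by category**

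| Safety item | Stated handling | Needs a causality judgement? |
|---|---|---|
| All-cause adverse events | Summary tabulation | No |
| Adverse drug reactions, including suspected unexpected serious ones | Compared between groups | Yes |
| Safety laboratory values | Mixed model with treatment-by-visit | No |

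Among adverse events, the comparison is thus assigned to the one category that needs the judgement.

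**How attribution enters**

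Let r be the proportion of women with an event in an arm and a the share of those women whose event is attributed to a drug. The compared proportion is r × a. Two arms with equal r differ on this measure whenever a differs.

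*Inputs.* 200 women at 1:1 give 200 / 2 = 100 per arm (Number of participants; Study design). The values of r and a are assumptions. So is the yardstick, a two-sided 5% Fisher exact test, because the article names no test here.

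*Formula.* The probability of a significant result is the sum, over all counts i and j from 0 to 100, of Bin(i; 100, r × a₁) × Bin(j; 100, r × a₀), taken where the Fisher p-value for i/100 versus j/100 is at most 0.05.

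*Example at r = 20%.* Attribution of 30% versus 10% gives 0.20 × 0.30 = 6% against 0.20 × 0.10 = 2%. Attribution of 30% versus 0% gives 6% against 0%.

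Probability of a significant difference when true event rates are equal:

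| Attributed share, one arm v other | r = 10% | r = 20% | r = 30% |
|---|---|---|---|
| 30% v 30% | 0.01 | 0.02 | 0.03 |
| 30% v 20% | 0.02 | 0.05 | 0.08 |
| 30% v 10% | 0.03 | 0.17 | 0.33 |
| 30% v 0% | 0.08 | 0.56 | 0.90 |

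The table is symmetric in the arms, so the excess may fall on either side.

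*Masking.* A real difference can also disappear. If 20% of the infusion arm and 30% of standard care had events, with attribution of 30% and 20% respectively, the compared proportions would be 0.20 × 0.30 = 6% and 0.30 × 0.20 = 6%.

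**The case against.** The other side has several sound points.

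- **Other safety comparisons exist.** A reader might infer that reactions are the only safety contrast between groups. They are not: the safety laboratory values go through the mixed model and need no causality judgement. The point is confined to adverse events.
- **Standard care is not drug-free.** A reader might also infer that a reaction can only be a reaction to a drug that the infusion arm alone receives, so that the imbalance is built in. The text does not say so. It speaks of adverse drug reactions in general, calls standard care an active comparator, describes it as typically oral iron, and cites gastrointestinal side effects of oral iron in up to 30% in earlier trials. Control-arm reactions can be counted and could even be the more frequent.
- **No test is stated.** The two-sided 5% rule in the article is for efficacy endpoints. It would be wrong to describe the reactions as formally tested.
- **All-cause events are reported.** They are tabulated, and gastrointestinal symptoms are a separate outcome. A reader could set the arms side by side if the table is given by arm, as is usual.
- **Details may lie elsewhere.** The definition of a reaction, the assessor and any test may be in the full protocol or analysis plan, which are not shown. Their absence from the article is not counted as a fault here. The article also does not say who judges relatedness.
- **The illustration is assumed.** With 30% versus 20% attribution the probability of a false difference is only 0.02 to 0.08. Expected counts of 6/100 versus 1/100 would give a two-sided Fisher p of 0.12.

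All of this limits the size and wording of the point. It does not change the fact that the article itself selects which adverse-event category is compared, and selects the one that depends on judgement.

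**Conclusion.** The point stands as a minor one. Within adverse events, the stated between-group comparison rests on a causality judgement in an open-label trial with two very different exposures, and it is narrower than the declared safety outcome. It can be biased in either direction.

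The size cannot be derived from the document. On the assumed figures it runs from negligible, when attribution is similar in the two arms, to large only when events in one arm are hardly ever attributed to a drug. Nothing in the article says that this second case applies. The conclusion assumes that the person judging relatedness can know the arm, which follows from the open-label design but is not spelled out for this step.

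**What to change.** Make the main between-group adverse-event comparison the number of participants with any adverse event, and with any serious adverse event, from randomisation to week 12, regardless of causality, by arm, with the risk difference and its 95% confidence interval.

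Keep adverse drug reactions and suspected unexpected serious adverse reactions as a descriptive summary by arm, and state the reference drug for the causality judgement in each arm.

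The cost is a change of wording and one extra table; adverse events are already collected. The downside is that an all-cause comparison is less specific to drug effects, because it includes events unrelated to any iron product. The descriptive summary of reactions keeps that more specific view available.
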